### Sample size

As this is a pilot feasibility study designed to estimate the effect size and variance of the primary outcome for a future definitive trial, no formal hypothesis-testing power calculation was performed. The sample size was determined with reference to previous multicenter randomized controlled trial of acupuncture for menstruation-related migraine (16, 17), which provided reference effect size estimates and variability data for this population. Based on the effect size reported in previous high-quality trials and clinical feasibility, we determined that 30 participants per group would provide a valid estimate of treatment response, variability, and retention (18). Assuming a 20% dropout rate during the trial, we planned to enroll 38 participants per group, with a total target sample size of 76. This sample size is sufficient to estimate key feasibility parameters and provides a preliminary basis for the design and sample size calculation of future confirmatory trials.

### Recruitment

#### Recruitment strategy

Participant recruitment will be conducted at the Chengdu Pidu District Hospital of Traditional Chinese Medicine over an estimated period of 12 months. A multi-pronged strategy will be employed to ensure efficient and ethical enrollment:

Clinical Referral: Primary recruitment will occur through the hospital’s Neurology, Gynecology, and Acupuncture outpatient departments. Board-certified neurologists, gynecologists, and acupuncturists will be informed about the study and will identify potential eligible patients during routine consultations.

Hospital advertising: Research posters and brochures that have undergone ethical review and include key inclusion criteria and contact information will be displayed in prominent locations within the hospital, such as waiting areas and relevant clinical departments.

Community Outreach: Advertisements will be placed on the hospital’s official website and social media platforms (e.g., WeChat public account), targeting women of reproductive age in the local community. All advertisements will be reviewed and approved by the IRB.

#### Recruitment process

The recruitment process will follow a standardized, stepwise procedure to ensure proper screening and informed consent:

Initial Screening: Potentially eligible individuals expressing interest will undergo a preliminary screening, usually via phone or in-person, using a standardized checklist based on the core inclusion/exclusion criteria (e.g., age, headache diagnosis, menstrual cycle regularity).

Informed Consent: Eligible participants will receive a detailed informed consent form approved by the Institutional Review Board. A trained researcher will explain the purpose of the study, the study procedures, potential risks and benefits, the randomization method, and the participant’s right to withdraw from the study at any time without compromising their medical care. Participants will be given ample time (≥24 h) to consider whether to participate and to ask questions before signing the written informed consent form.

Enrollment and Screening Phase: After signing the informed consent form, participants will be formally enrolled and assigned a unique study identification number. Subsequently, they will enter a three-cycle screening phase lasting approximately 12 weeks, during which they must complete a daily headache diary to confirm a diagnosis of PMM or MRM based on the ICHD-3 appendix criteria. During this screening phase, participants will undergo blood draws at specific phases (early follicular and mid-luteal) in each of the qualified cycles, and heart rate variability monitoring.

Diagnostic Confirmation and Baseline Data Extraction: Once participants have completed headache diary entries for all three cycles, two independent neurologists will review the diary data to confirm the diagnosis of PMM or MRM. Baseline data for the primary outcome measures will be extracted from the headache diary of the qualified screening cycles (averaged) only after the diagnosis has been confirmed. Participants who do not meet the diagnostic criteria will be excluded from randomization.

Randomization: Eligible participants who have completed the screening period and whose prospective diary data confirm the diagnosis of PMM or MRM (i.e., at least 2 of the 3 screening cycles meet the predefined headache frequency criterion of 2–14 moderate-to-severe headache days) will be randomly allocated in a 1:1 ratio to the press-needle group or the naproxen sodium group. Participants who do not meet this diagnostic confirmation will be excluded from randomization. Baseline values for the primary outcome will be derived from the average of all qualified screening cycles (those with 2–14 moderate-to-severe headache days), ensuring that the baseline reflects the participant’s typical headache burden rather than a single potentially atypical cycle.

#### Risk–benefit assessment

The risks associated with trial participation are considered minimal to low, as all procedures (press-needle therapy, blood sampling, questionnaires, autonomic and optional imaging assessments) are routine and possess well-established safety profiles. Potential direct benefits for participants include headache relief and improved quality of life, while the study aims to generate valuable scientific knowledge. The favorable risk–benefit profile has been approved by the IRB. All potential risks and benefits are thoroughly disclosed in the informed consent process.

#### Allocation of interventions

Participants who meet all eligibility criteria and provide written informed consent will be formally enrolled and assigned a unique study identification number. A computerized block randomization sequence with a 1:1 allocation ratio (Experimental Group: Control Group) will be generated by an independent statistician not involved in recruitment or intervention delivery, using random block sizes of 4 and 6. The allocation sequence will be concealed using sequentially numbered, opaque, sealed envelopes (SNOSE). Upon enrollment and completion of baseline assessments, the treating acupuncturist will open the next sequentially numbered envelope in the presence of the participant to reveal the group assignment. This process ensures allocation concealment.

#### Data collection and management

Data will be collected using a combination of electronic and paper-based Case Report Forms (eCRFs/pCRFs).

Electronic Data: Primary outcome data (daily headache diary) will be collected via a secure, validated electronic patient-reported outcome (ePRO) system with daily reminders. HRV raw data will be exported from the dedicated device software.

Paper-based Forms: Secondary outcome questionnaires (MMFIQ, MSQ) and safety monitoring forms will be completed on paper during clinic visits and subsequently entered into a dedicated Electronic Data Capture (EDC) system by trained research staff.

Data Management: All data will be entered twice (double data entry) into a password-protected, audit-trail enabled EDC system (e.g., REDCap). Range and logic checks will be programmed to ensure data quality. Regular data monitoring visits will be conducted to verify source data against eCRFs. The final trial database will be locked after resolution of all queries and before statistical analysis.

#### Quality control

Standardized Training: All investigators and research staff will undergo protocol-specific training prior to trial initiation, covering recruitment procedures, intervention protocols, outcome assessment, data entry, and Good Clinical Practice (GCP) guidelines.

Treatment Fidelity: Acupuncturists will follow a detailed treatment manual. Random audits of treatment sessions (e.g., photo verification of point location) will be performed.

Data Monitoring: An independent Data Monitoring Committee (DMC) is not established for this low-risk trial. Instead, the principal investigator and study coordinator will perform regular internal data reviews for completeness, consistency, and protocol adherence.

Protocol Adherence: Regular investigator meetings will be held to discuss protocol adherence and address any operational issues.

#### Confidentiality and ethics compliance

Confidentiality: All participant data will be identified only by a unique study ID. Personal identifying information will be stored separately from study data in a password-protected file accessible only to authorized personnel. All documents will be stored in locked cabinets or on secure servers.

Ethics Compliance: This protocol has been approved by the Ethics Committee of Chengdu Pidu District Hospital of Traditional Chinese Medicine (Approval No. K-2026-016). The trial will be conducted in full accordance with the principles of the Declaration of Helsinki and Chinese regulatory requirements. Any protocol amendments will require prior IRB approval.

#### Statistical methods

All analyses will be performed using both Intention-to-Treat (ITT) and Per-Protocol (PP) principles. A two-sided *p* < 0.05 will be considered statistically significant.

#### Analysis populations

Intention-to-Treat (ITT) Population: All randomized participants, analyzed according to their originally assigned group, regardless of protocol adherence or dropout.

Per-Protocol (PP) Population: A subset of the ITT population comprising participants who completed at least 80% of the planned treatment courses (all three cycles with 4 sessions per cycle), provided valid primary outcome data at the end of the intervention period, and had no major protocol violations.

#### Handling of missing data

The pattern and mechanism of missing data will be examined using descriptive statistics and graphical methods. For the primary outcome, if missing data are judged to be Missing At Random (MAR), multiple imputation (MI) by chained equations will be applied to generate 5 imputed datasets. Auxiliary variables supporting the MAR assumption will include baseline moderate-to-severe headache days, age, migraine subtype (pure menstrual migraine vs. menstrually-related migraine), baseline heart rate variability indices, and treatment adherence levels to improve imputation precision and robustness. Sensitivity analyses will compare MI results with complete-case analysis. To further assess the robustness of results against potential departures from the MAR assumption, a sensitivity analysis under the Missing Not At Random (MNAR) framework will be conducted using a delta-adjusted multiple imputation approach, assuming progressively larger shifts in headache days for participants with missing primary outcome data. For secondary continuous outcomes, mixed-effects models for repeated measures (MMRM) will be used, which provide valid estimates under the MAR assumption using all available data.

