### Eligibility criteria

#### Inclusion criteria

Meets the diagnostic criteria for “migraine without aura” (ICHD-3 code 1.1)” as defined in the International Classification of Headache Disorders, 3rd Edition (ICHD-3);Meets the diagnostic criteria for “pure menstrual migraine” (A1.1.1) or “menstrually-related migraine” (A1.1.2) as outlined in the appendix to the ICHD-3, and this diagnosis has been validated by a prospective headache diary covering three consecutive menstrual cycles;Age 18–45 years, with a normal menstrual cycle of 28 ± 7 days and a menstrual duration of 3–7 days;During the 3-cycle screening period, at least 2 of the 3 menstrual cycles have 2–14 days with moderate-to-severe headache (NRS ≥ 4) per cycle (meeting the ICHD-3 appendix criterion for PMM or MRM). Baseline data for the primary outcome will be calculated as the average number of moderate-to-severe headache days across all qualified cycles (i.e., those cycles meeting the 2–14 day criterion) during the screening period;Complete the daily headache diary throughout the 3-cycle screening period (with a completion rate of ≥80% for daily entries within each menstrual cycle) to demonstrate good patient compliance;Voluntary signing of the informed consent form.

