#### Handling of multiple comparisons

This trial includes one primary outcome and multiple secondary/exploratory outcomes. The primary outcome is designated as the primary endpoint for this pilot study and will be analyzed at a pre-specified two-sided alpha level of 0.05 without adjustment for multiplicity. Given the exploratory nature of this trial, all results—including the primary outcome—will be interpreted descriptively rather than as confirmatory evidence. No adjustment for multiple comparisons will be performed for any secondary or exploratory outcomes (headache intensity, functional impact, quality of life, acute medication use, heart rate variability indices, serum biomarkers, neuroimaging metrics). All these outcomes are designated as exploratory, and their results will be interpreted strictly as hypothesis-generating rather than confirmatory. This approach prioritizes sensitivity and hypothesis discovery over strict control of the family-wise error rate, and any positive findings will require confirmation in future adequately powered trials.

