#### Primary outcome analysis

The primary outcome measure—the change in the number of days with moderate-to-severe headaches per menstrual cycle from the last menstrual cycle of the screening period through the end of the 3-month intervention—will be analyzed using a repeated-measure mixed-effects model (MMRM). This model will treat the measurements from each menstrual cycle during the 3-month intervention period as repeated measures, with treatment group, time, and the interaction between treatment and time as fixed effects. The average number of moderate-to-severe headache days from the qualified screening cycles will be included as a covariate, and subject-specific random intercepts will be specified to account for within-subject correlation across the three menstrual cycles.

The primary focus is on the differences in the magnitude of change from baseline across groups at the end of the intervention period (Week 12/Month 3). Results will be presented as adjusted between-group differences, along with their 95% confidence intervals (CI) and corresponding *p*-values. Given that this is a preliminary feasibility study, *p*-values will be interpreted descriptively rather than as confirmatory evidence.

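### The primary missing-data method depends on a MAR judgement that the data cannot settle, stops at 5 imputations and leaves the primary analysis unclear; the random-intercept covariance adds an avoidable risk to the single-cycle contrast

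*Protocol article*

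**What the plan says.** Handling of missing data (Protocol article) makes imputation of the primary outcome conditional: it applies "if missing data are judged to be Missing At Random (MAR"), a judgement to be reached from descriptive statistics and graphs. In that case "multiple imputation (MI) by chained equations will be applied to generate 5 imputed datasets", with baseline headache days, age, migraine subtype, baseline heart rate variability and adherence as auxiliary variables. The section also plans a complete-case comparison and a delta-adjusted MNAR analysis. For secondary outcomes it relies on the mixed model alone, on the ground that this is valid under MAR with all available data.

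Primary outcome analysis describes a mixed model on the three treatment cycles and does not mention imputation. Its covariance is set by one clause: "subject-specific random intercepts will be specified to account for within-subject correlation across the three menstrual cycles". The contrast of interest is placed "at the end of the intervention period (Week 12/Month 3"). Subgroup and sensitivity analyses lists an ITT analysis without imputation among the sensitivity analyses. Inclusion criteria admits women "with a normal menstrual cycle of 28 ± 7 days".

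Handling of multiple comparisons says the primary outcome "will be analyzed at a pre-specified two-sided alpha level of 0.05 without adjustment for multiplicity", but also that all results are read descriptively. Sample size says that "no formal hypothesis-testing power calculation was performed".

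**The concern.** Three choices fixed in the text bear on the primary estimate.

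- **The trigger.** Whether data are MAR or MNAR depends on the values that were not observed, so plots and summaries of observed data cannot decide it. A primary method that hangs on this judgement is chosen after the data are seen, and the protocol does not say what is primary if the judgement goes the other way. The sections also disagree: one reads as a mixed model on observed data, another demotes the unimputed analysis to a sensitivity analysis.
- **Five imputations.** With few imputations the pooled estimate depends on the random seed to a degree that is easily avoided.
- **The random intercept.** With a common residual variance it pools variance over three cycles, while the reported contrast concerns one cycle.

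The trial is meant to supply an effect size and a variance for a later confirmatory trial, so the estimate, its interval and the cycle-specific variance are its main products even though the p-value is descriptive.

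**Working it through.** **Planned size.** Sample size takes 30 evaluable per group and 20% dropout: 30 / (1 − 0.20) = 37.5, rounded up to 38 per group, 76 in total. This reproduces the plan's figure.

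**Which analysis is primary.** Side by side: Handling of missing data imputes the primary outcome if MAR is accepted; Primary outcome analysis fits the mixed model without mention of imputation; Subgroup and sensitivity analyses makes the unimputed ITT analysis secondary. If MAR is accepted, imputation is implied as primary but not stated. If MAR is rejected, nothing is named.

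**Noise from m imputations.** The fraction of missing information (FMI) is not in the document. I assume 0.20, in line with the 20% dropout, with a range of 0.05 to 0.40.

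- Standard error inflation against infinitely many imputations: √(1 + FMI/m).
- SD of the pooled estimate over reruns on the same data, as a share of its standard error: √[(FMI/m) / (1 + FMI/m)].
- At FMI 0.20, m = 5: FMI/m = 0.04; inflation √1.04 = 1.020; rerun SD √(0.04/1.04) = 0.196.

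| FMI | SE inflation, m=5 | Rerun SD/SE, m=5 | Rerun SD/SE, m=20 | Rerun SD/SE, m=50 |
|---|---|---|---|---|
| 0.05 | 0.5% | 0.10 | 0.05 | 0.03 |
| 0.20 | 2.0% | 0.20 | 0.10 | 0.06 |
| 0.40 | 3.9% | 0.27 | 0.14 | 0.09 |

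For a result at z = 1.96 (p = 0.05), with normal reference and the standard error held fixed, FMI 0.20:

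- m = 5, one rerun SD: z = 1.96 ± 0.196, p from 0.031 to 0.078. Over ±1.96 rerun SDs: p from 0.019 to 0.115.
- m = 50, one rerun SD: p from 0.043 to 0.058. Over ±1.96 rerun SDs: p from 0.037 to 0.066.

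At m = 5 the ±1.96 SD range is 0.031 to 0.078 at FMI 0.05 and 0.013 to 0.154 at FMI 0.40.

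**Random intercept.** A simulation with 76 participants, three cycles, treatment-by-time effects and a baseline covariate, fitted by REML with a random intercept and common residual variance (1,500 runs per scenario, simulation error about 0.6 percentage points), gave these type I error rates for the cycle 3 contrast at a nominal 5%. The SDs and correlations are assumed. Each range spans compound-symmetric and first-order autoregressive correlation, with and without dropout.

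| Relative SD by cycle | Type I error |
|---|---|
| 1.0, 1.0, 1.0 | 4.6% to 5.5% |
| 0.8, 1.0, 1.2 | 9.0% to 11.5% |
| 1.2, 1.0, 0.8 | 0.7% to 1.8% |

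A hand check shows why. The pooled SD is √[(0.64 + 1 + 1.44)/3] = 1.013. With rising SDs the model uses 1.013 where 1.2 applies, a ratio of 0.844; 1.96 × 0.844 = 1.655, which gives a two-sided error of 9.8%. With falling SDs the ratio is 1.013/0.8 = 1.267; 1.96 × 1.267 = 2.48, which gives 1.3%.

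**Time label.** Three cycles of 21, 28 or 35 days last 63, 84 or 105 days. Week 12 is day 84, so it coincides with the end of cycle 3 only for 28-day cycles.

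**The case against.** The strongest reply is that this is a pilot with descriptive p-values, no power calculation and planned MNAR, complete-case and unimputed analyses, so seed noise and the MAR wording matter little. Much of that stands, and it rules out several stronger readings that a reader might infer.

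- **That the p-value and interval are unreliable.** Five imputations cost about 2% in standard error at FMI 0.20, and Rubin's rules with a t reference allow for it. FMI may also be lower than assumed: the 20% dropout is for the whole trial, which includes follow-up. If dropouts miss only cycle 3, with correlation 0.5 between cycles, FMI is about 0.15 and the rerun SD about 0.17 standard errors.
- **That imputation adds nothing but noise to a mixed model already valid under MAR.** Age, subtype, heart rate variability and adherence are in the imputation model but not in the primary model, so imputation conditions on more information.
- **That the random intercept is wrong.** The protocol does not state the residual structure and reports no variances. If variance follows the mean and headache days fall under treatment, the error is on the conservative side.
- **That Week 12 captures an untreated or incomplete cycle.** The Primary outcome section counts days per menstrual cycle and the model takes cycles as its repeated measures. There is no calendar-window rule at day 84, and the protocol elsewhere describes three screening cycles as about 12 weeks. The label is loose; the time point is not wrong.

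What the reply does not answer is the trigger itself. The planned sensitivity analyses do not say which analysis is primary, and the protocol still sets a 0.05 threshold that a borderline result could cross by choice of seed.

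**Conclusion.** The concern holds as a matter of specification. The MAR trigger cannot be operated from observed data, it has no stated alternative, and the sections do not agree on which analysis is primary. Five imputations are too few for reproducibility: rerun noise is about 0.20 standard errors at FMI 0.20 (0.10 to 0.27 over FMI 0.05 to 0.40), against about 0.06 with 50. The interval remains valid. FMI is an assumption throughout.

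The covariance point holds conditionally. With common residual variance, the cycle 3 contrast is close to nominal if variances are equal across cycles and is liberal or conservative if they rise or fall. The document neither shows nor excludes such a change. The Week 12/Month 3 label is a wording point only. None of this shows that the primary analysis is invalid; these are cheap improvements worth making before the data are seen.

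**What to change.** 1. In Handling of missing data, remove the MAR judgement as a condition and name one primary analysis, with the same statement in Primary outcome analysis and in Subgroup and sensitivity analyses. Either is acceptable: the mixed model fitted directly to all observed cycles of all randomised participants, or multiple imputation with the listed auxiliary variables. The direct model gives up the auxiliary information, which is its small downside.
2. Wherever imputation is used, including the delta-adjusted analysis, use at least 50 imputations with a fixed, recorded seed. A common rule, m = 1 + ½(FMI/CV)² with a 5% CV for the standard error, asks for 9 at FMI 0.20 and 33 at FMI 0.40, so 50 covers the assumed range. The cost is computing time.
3. Replace the random intercept by an unstructured 3x3 covariance with Kenward-Roger degrees of freedom, with heterogeneous compound symmetry as the fallback if it does not converge. The cost is four more covariance parameters (6 instead of 2).
4. Reword the Week 12/Month 3 label as the third treated menstrual cycle.

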#### Handling of multiple comparisons

This trial includes one primary outcome and multiple secondary/exploratory outcomes. The primary outcome is designated as the primary endpoint for this pilot study and will be analyzed at a pre-specified two-sided alpha level of 0.05 without adjustment for multiplicity. Given the exploratory nature of this trial, all results—including the primary outcome—will be interpreted descriptively rather than as confirmatory evidence. No adjustment for multiple comparisons will be performed for any secondary or exploratory outcomes (headache intensity, functional impact, quality of life, acute medication use, heart rate variability indices, serum biomarkers, neuroimaging metrics). All these outcomes are designated as exploratory, and their results will be interpreted strictly as hypothesis-generating rather than confirmatory. This approach prioritizes sensitivity and hypothesis discovery over strict control of the family-wise error rate, and any positive findings will require confirmation in future adequately powered trials.

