#### Neuroimaging markers

Procedure: Structural and functional brain MRI will be performed at baseline and end of the 3-month intervention.

Image Acquisition: All scans will be conducted on a 3.0 Tesla MRI scanner using a standardized protocol, including:

High-Resolution 3D T1-Weighted Imaging: For voxel-based morphometry (VBM) analysis to evaluate regional gray matter volume changes in pain-processing (e.g., insula, anterior cingulate cortex) and autonomic regulation (e.g., hypothalamus, brainstem) regions;

Resting-State Functional MRI (rs-fMRI): 8-min eyes-closed scan optimized for blood-oxygen-level-dependent (BOLD) signal detection.

Assessment Timepoints: Baseline and end of Treatment Months 1–3.

Image Analysis: Preprocessing (motion correction, spatial normalization, smoothing) and statistical analysis will follow standard pipelines. Seed-based correlation analysis and independent component analysis (ICA) will evaluate functional connectivity alterations within/between the Salience Network and Central Autonomic Network.

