#### Exploratory and safety analyses

Exploratory Biomarkers/Imaging: Changes in serum biomarker levels (CGRP, estradiol, progesterone) and neuroimaging metrics will be analyzed using paired t-tests or Wilcoxon signed-rank tests within each group, and between-group comparisons will be made using ANCOVA. Correlation analyses (Pearson’s or Spearman’s) will explore relationships between clinical, autonomic, and biomarker/imaging changes. All exploratory findings will be reported with effect sizes and 95% CIs, and will be explicitly labeled as “exploratory, unadjusted for multiple comparisons, for hypothesis generation only” to prevent overinterpretation.

Safety Analyses: The incidence of adverse events (AEs) and serious adverse events (SAEs) will be summarized by treatment group, described by system organ class and preferred term. Differences in AE rates will be compared using Fisher’s exact test.

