Mechanistically, we anticipate that this stage-specific intervention will modulate pain-related brain networks and autonomic regulatory circuits. A growing body of neuroimaging evidence suggests that acupuncture can modulate functional connectivity in pain-processing regions, including the amygdala, insula, mesolimbic-parietal cortex, and temporal cortex (41), and can modulate the hypothalamic-limbic-brainstem circuit involved in autonomic control (23, 39, 42). Acupuncture has been shown to enhance connectivity between the amygdala/mediofrontal-parietal cortex and the middle temporal gyrus, as well as between the mediofrontal-parietal cortex and the superior temporal gyrus—regions that play a key role in multisensory pain modulation (41). Furthermore, a meta-analysis of resting-state fMRI studies further confirmed that acupuncture modulates the superior frontal gyrus, angular gyrus, and corpus callosum in migraine patients, and these changes are significantly associated with reduced pain intensity and headache frequency (43). Furthermore, the sustained preventive effects of acupuncture appear to involve influences on the default mode network, the anterior parietal network, the limbic system, and the descending pain modulation system (44). If these imaging changes are observed, they are expected to correlate with reduced headache frequency and improved autonomic balance, providing preliminary evidence for the central mechanisms of sequential pressure acupuncture therapy.

Compared to the control group receiving oral naproxen sodium, the sequential acupuncture therapy in the experimental group—as a non-pharmacological preventive measure—not only demonstrated better tolerability but also allowed for personalized, phased interventions tailored to the cyclical nature of menstrual migraines, aligning closely with the pathophysiological changes of the condition. This therapy avoids the gastrointestinal discomfort, neurological adverse reactions, and potential safety risks associated with long-term use of oral naproxen sodium (45). Unlike existing studies that focus solely on subjective clinical efficacy, this study innovatively integrates multidimensional assessments of objective autonomic nervous system function, serum biomarkers, and neuroimaging to systematically explore the core therapeutic mechanisms of sequential acupuncture therapy.

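### The blanket no-adjustment rule covers neuroimaging and does not separate multiplicity across outcomes from multiplicity within a single brain map

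*Protocol article*

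**What the plan says.** Under Statistical methods, one threshold is set for all analyses: "A two-sided *p* < 0.05 will be considered statistically significant".

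Handling of multiple comparisons then says "No adjustment for multiple comparisons will be performed for any secondary or exploratory outcomes". Its list of covered outcomes ends with "heart rate variability indices, serum biomarkers, neuroimaging metrics". Exploratory and safety analyses repeats the rule for biomarkers and imaging, whose findings are to be labelled "exploratory, unadjusted for multiple comparisons, for hypothesis generation only". It also says how they are tested: they "will be analyzed using paired t-tests or Wilcoxon signed-rank tests within each group, and between-group comparisons will be made using ANCOVA".

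The imaging itself is described under Neuroimaging markers. Voxel-based morphometry (VBM) is used "to evaluate regional gray matter volume changes in pain-processing (e.g., insula, anterior cingulate cortex) and autonomic regulation (e.g., hypothalamus, brainstem) regions". For resting-state data, "Seed-based correlation analysis and independent component analysis (ICA) will evaluate functional connectivity alterations" within and between two named networks, the Salience Network and the Central Autonomic Network. Preprocessing and statistical analysis are to follow standard pipelines, which are not described further. Table 2 shows MRI in a subset whose size is not given.

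The third aim under Objectives is to explore mechanisms with autonomic, serological and neuroimaging markers. The Discussion adds: "If these imaging changes are observed, they are expected to correlate with reduced headache frequency and improved autonomic balance", and says this would provide preliminary evidence of central mechanisms.

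**The concern.** Two kinds of multiplicity fall under one rule. The first is across outcomes: a functional-impact score, SDNN and CGRP are each one test, and a pilot may reasonably report them unadjusted and say so. The second is within one image analysis: a VBM map, a seed-based connectivity map or an ICA component map is a large family of tests reported as a single result. The rule names neuroimaging and makes no exception for the second kind.

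This is a stated rule, so it cannot be set aside as detail left to an analysis plan. An analysis plan that followed it literally could not add within-map correction; one that added such correction would contradict the protocol. The reference to standard pipelines does not settle the matter, because those pipelines may or may not include voxel- or cluster-level correction, and if they do, they conflict with the rule.

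What is at stake is whether the imaging results can guide the next trial. The rule is justified as favouring hypothesis discovery, but a map that is nearly sure to show something when nothing is happening gives little basis for choosing a hypothesis. An exploratory label tells the reader to be cautious; it does not change that error rate.

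**Working it through.** **The plan's own figures.** The article gives no error rate for imaging and no number of imaging tests, so there is no imaging figure to reproduce. The one computed design figure, the sample size, does reproduce: 30 / (1 − 0.20) = 37.5, rounded up to 38 per group, 76 in total. It does not enter the check below.

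**Inputs from the article.** Two-sided alpha 0.05; no adjustment; four VBM regions named as examples (insula, anterior cingulate, hypothalamus, brainstem), with the list left open; seeds, components and connections not counted; three contrasts per metric (two within-group, one between-group).

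**Assumptions not in the article.** Number of regions tested (4, 10 or 20); correlation between region tests (0 to 0.7); for maps, 3 mm voxels, a brain-sized mask of 56,864 voxels, and smoothness of 8 to 24 mm FWHM.

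**Case A: region summaries only.** With m independent tests and no effect, the chance of at least one p < 0.05 in a contrast is 1 − (1 − 0.05)^m:

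- m = 4: 1 − 0.95^4 = 0.19
- m = 10: 1 − 0.95^10 = 0.40
- m = 20: 1 − 0.95^20 = 0.64

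Correlation lowers these. Simulation of equally correlated normal test statistics (40,000 runs each) gave:

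| Regions | Corr. 0.3 | Corr. 0.5 | Corr. 0.7 |
|---|---|---|---|
| 4 | 0.17 | 0.16 | 0.13 |
| 10 | 0.35 | 0.29 | 0.21 |
| 20 | 0.54 | 0.42 | 0.29 |

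So even with only the four example regions, the rate is 0.13 / 0.05 = 2.6 to 0.19 / 0.05 = 3.8 times nominal. Equally, 81% to 87% of such null contrasts would show nothing.

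**Case B: voxelwise testing of a brain-sized map.** Smooth Gaussian fields with no effect, 120 runs at each smoothness:

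| FWHM (mm) | Any voxel at p < 0.05 | Any voxel at p < 0.001 | Mean share of voxels at p < 0.05 |
|---|---|---|---|
| 8 | 1.00 | 1.00 | 5.0% |
| 12 | 1.00 | 1.00 | 5.1% |
| 16 | 1.00 | 1.00 | 5.0% |
| 24 | 1.00 | 0.78 | 5.0% |

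A voxelwise search confined to a few regions was not simulated; it has fewer effective tests than the brain-sized mask.

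**After correction.** With Bonferroni control inside one family of independent tests, the rate is 1 − (1 − 0.05/m)^m = 0.049 for m = 4, 10 or 20, against 0.19, 0.40 and 0.64 unadjusted.

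**The case against.** The best reply is that the rule was meant for scalar summaries. It lists neuroimaging beside single-score outcomes. The prescribed tests are paired t-tests, Wilcoxon tests, ANCOVA and simple correlations, with effect sizes and confidence intervals. Comprehensive mechanism analysis gives connectivity strength in the target network as its imaging example, which is a single number per participant. Map-level work sits in its own section under standard pipelines. On this reading the rule governs comparisons across outcomes and the pipelines govern the maps. This reading is plausible, and it is why Case A belongs beside Case B. But the article does not state it, the VBM region list is open-ended, and VBM is voxel-based by name.

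The safeguards are also real: positives are said to need confirmation, and the labelling is meant to prevent overinterpretation. They limit what will be claimed, but leave the error rate unchanged.

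A reader might infer more than the text supports:

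- **That whole-brain testing is planned.** The article never says so; it points to regions and two networks.
- **That every imaging contrast will show significant regions.** This holds only for voxelwise or very many-region testing, as Case A shows.
- **That the mechanism objective cannot come out negative.** It also rests on heart rate variability and on CGRP, estradiol and progesterone, any of which can be null, and it sets no success criterion.
- **That regions will be picked because they crossed an uncorrected threshold and then correlated with clinical change.** Nothing bars this, but no section plans it.

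**Conclusion.** The point holds as a defect of wording with a measurable consequence. The rule permits uncorrected testing within a map, and it conflicts with the standard pipelines if those include map-level correction; the article does not say which governs. Depending on how the analysis is done, the chance of a false positive in a null contrast runs from about 0.13 (four region summaries, correlation 0.7) to near certainty (brain-sized voxelwise map at uncorrected 0.05). That range rests on the assumptions listed above, because the article gives neither the number of tests nor the image parameters.

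The harm is confined to the imaging part of the third objective. The primary outcome, heart rate variability and serum markers are unaffected, and leaving separate exploratory outcomes unadjusted in a pilot is not an error. Because imaging is exploratory and done in a subset, the severity is minor.

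**What to change.** 1. In Handling of multiple comparisons and in Exploratory and safety analyses, limit the no-adjustment rule to comparisons across separate outcomes or scalar summaries.
2. State that any voxelwise or edgewise analysis is corrected within the map at 0.05, by cluster-level family-wise error, permutation with threshold-free cluster enhancement (TFCE), or false discovery rate. Alternatively, restrict imaging to a closed, pre-named list of regions and connections. Align Neuroimaging markers with whichever is chosen.
3. In the correlation analyses, use only pre-named measures from the Salience Network and Central Autonomic Network.

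This changes wording only and needs no new data. The cost is that fewer regions will be reported and sensitivity in the MRI subset will be lower.
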